## Abstract

**Background:**

The trial investigates the efficacy of internet-based cognitive behavioral therapy (iCBT) in improving health-related QoL in patients with endometriosis, which is a chronic gynecological condition affecting up to 15% of people with female-assigned reproductive organs. Endometriosis is stress-related and comes with various physical symptoms such as pelvic pain and infertility. It has a substantial impact on health-related quality of life (QoL), and mind-body interventions seem promising in reducing the psychological burden.

**Methods:**

This is a monocentric randomized-controlled trial recruiting 120 patients with endometriosis. The intervention consists of eight iCBT modules focusing on psychoeducation, cognitive restructuring, pacing, and emotion regulation. Participants will receive written feedback from a trained therapist weekly. The comparator is a waitlist control group. All participants will be followed up 3 months after the intervention, and the intervention group will additionally be followed up 12 months after the intervention. Trial participants will not be blinded to the allocated trial arm. Primary outcome measures are endometriosis-related QoL, pain, and pain-related disability. Secondary outcomes include coping, illness representations, and psychological flexibility. Statistical analyses will be performed following intention-to-treat principles.

**Discussion:**

This randomized-controlled trial is the first trial to test the efficacy of iCBT for improving endometriosis-related QoL. Potential predictor variables and key mechanisms in treatment will be investigated to enable further progression in medical and psychological care for patients with endometriosis.

**Trial registration:**

ClinicalTrials.gov, NCT05098444 Registered on October 28, 2021

## Administrative information

Note: the numbers in curly brackets in this protocol refer to SPIRIT checklist item numbers. The order of the items has been modified to group similar items (see http://www.equator-network.org/reporting-guidelines/spirit-2013-statement-defining-standard-protocol-items-for-clinical-trials/).

## Introduction

### Background and rationale {6a}

#### Background

Endometriosis, defined by the presence of endometrial-like tissue outside the uterine cavity, is an inflammatory, chronic disease often associated with pelvic pain [1], infertility [2], and reduced quality of life (QoL) [3]. Prevalence of 5% up to 15% in women of reproductive age has been reported [4–6]. The societal and economic burden of endometriosis is severe, with high costs for medical treatment, reduced productivity at work [7], and high rates of absence from work [8]. The diagnosis of endometriosis is obtained only through laparoscopic surgery and histological confirmation. Due to a wide array of symptoms (both cyclic and acyclic [9]) and lack of awareness [10], practitioners often experience difficulties in diagnosing endometriosis correctly and in a timely manner [11]. This can lead to diagnostic delays of up to 10 years [12, 13] and prevents patients from receiving adequate treatment, adding further distress to the experienced psychological burden. Endometriosis is associated with symptoms of depression, anxiety [14, 15], and heightened feelings of uncertainty [16], leading to substantial reduction [3] in health-related quality of life (HRQoL). Dyspareunia, infertility, or decreased general ability to cope with everyday life [17] might put a strain especially on intimate relationships [18], impairing relationship satisfaction [19], and adding to the social burden of endometriosis [20]. The presentation of physical symptoms seems consistent across populations with different cultural backgrounds and geographical locations [7, 21]. However, HRQoL might be further reduced by culturally specific societal expectations, with, for example, women of Arab ancestry in the Middle Eastern region experiencing greater distress when suffering from infertility [22].

The exact etiology and pathogenesis of endometriosis remain unclear, although some biological and psychosomatic mechanisms and circuits involved in the progression of endometriosis have been identified: endometriosis is stress-related, with symptoms of endometriosis causing an increase in perceived psychological stress [23, 24] as well as high levels of chronic stress promoting overregulation of the hypothalamic–pituitary–adrenal (HPA) axis [25], leading to chronic inflammatory dysregulation and further growth of endometriotic lesions [26]. Chronic inflammation contributes to enhanced sensibility of nociceptive afferents [27], supporting peripheral and central sensitization processes [28] in regard to chronic pelvic pain (CPP) as one of the cardinal symptoms [1]. Overall, the complex pathogenesis might contribute to the existing knowledge gap regarding the precise mental health sequelae of endometriosis and unsubstantiated presumptions about the causality between physical and psychological symptoms [29].

There is no remedial treatment for patients with endometriosis available: it is a chronic disease with high recurrence rates after surgical or pharmacological treatment. Medical treatment of endometriosis is symptom-based, often focused on pain relief and treating infertility [30]. Surgical treatment is directed at ablating or excising endometriotic tissue. Pharmacological treatment is often directed at either symptomatic relief of pain through the use of analgesics (e.g., non-steroidal anti-inflammatory drugs) or at reducing circulating estrogen to a constantly lower level [31], leading to reduced ovarian function, less pain and inhibition in further growth of endometriotic tissue [32].

Given the high impact of endometriosis on HRQoL and the immediate influence of high psychological distress on its pathogenesis, developing complementary, non-medical treatment options for stress reduction and better psychological coping seems sensible. Diverse approaches have been tested over the last few decades. Different mind-body interventions for improving HRQoL in patients with endometriosis have been proven effective so far, including yoga [33], progressive muscle relaxation [33], and Traditional Chinese Medicine–based acupuncture combined with psychological consultations [35]. Kold, Hansen, Vedsted-Hansen, and Forman [36] conducted a prospective pilot single-arm trial, showing that mindfulness-based psychotherapy can lastingly improve HRQoL in patients with endometriosis. Yet overall, few studies have examined the effects of psychological and mind-body-interventions, most of them with limiting conclusions about efficacy due to rather low methodological quality (see [37, 38] for an overview).

#### Study rationale

There is an ongoing need for an evaluated, standardized, effective intervention for improving QoL in patients with endometriosis [39], although the exact interaction between physical and psychological symptoms is still to be further investigated. CBT teaches restructuring of unhelpful thoughts and core beliefs as well as behavioral activation and relaxation, leading to greater self-efficacy and enabling patients to display improved health behavior [40]. There is strong evidence for the effectiveness of CBT in treatment of chronic pain [41] and for stress reduction [42]. With perceived stress perpetuating experienced mental health sequelae and CPP as a cardinal symptom, we believe that the implementation CBT might be of great value for patients with endometriosis. Its efficacy in easing the burden of other disorders in women’s health (e.g., premenstrual dysphoric disorder [PMDD] [43]) further supports the implementation of CBT in treatment of endometriosis. Additionally, patients with endometriosis supported the implementation of CBT when informed about possible benefits [44]. However, to our knowledge, no study has yet investigated the effect of CBT in improving HRQoL in patients with endometriosis. We want to address this gap by testing the efficacy of CBT in improving HRQoL and examining potential moderators for new insights on key mechanisms in treatment.

An internet-based approach offers better accessibility alongside with reduced stigma associated with seeing a psychologist. Especially in patients with endometriosis, fear of not being taken seriously by a medical provider, fear of stigmatization, or disappointment in former practitioner-patient-relationships might otherwise hinder them from seeking psychological treatment [45]. We therefore decided to develop an internet-based CBT (iCBT) program. Such programs have previously been proven effective in the treatment of psychological [46] as well as psychosomatic [47] and somatopsychic [48] disorders and are considered as effective as face-to-face-therapy [49, 50]. We hypothesize that endometriosis-related QoL will be significantly improved when patients take part in our iCBT training.

### Objectives {7}

The trial objectives are:
To test the efficacy of iCBT in improving HRQoL in patients with endometriosisTo investigate potential predictor and mediator/moderator variables of treatment outcomesTo improve medical and psychological care for patients with endometriosis, whose symptoms are often dismissed by medical providersTo support further development of research within the field of women’s mental health with a clear focus on little-researched disorders relevant to people with female-assigned reproductive systemsTo foster the availability of online-interventions as a way of reducing barriers to appropriate care for patients with stigmatized diagnoses

### Trial design {8}

This is a randomized-controlled, two-armed, superiority trial testing the efficacy of an 8-week iCBT training in improving HRQoL in patients with endometriosis against a waitlist control group. Randomization will be balanced with a 1:1 ratio for patient allocation to the intervention group and waitlist control group. Identifying potential moderators and mediators of treatment outcome will also be a component of this trial.

## Methods: participants, interventions, and outcomes

### Study setting {9}

Patients with endometriosis will be recruited in Germany, and participants will access iCBT using their own technical devices (e.g., notebook, PC).

### Eligibility criteria {10}

The inclusion criteria are:
Endometriosis diagnosed through laparoscopic surgeryAge between 18 and 45Reduced HRQoL assessed with EHP-30 + 23 [52]Sufficient German language skillsAccess to an appropriate technical device (PC, laptop) with a stable internet connection

The exclusion criteria are:
Current diagnosis of one of the following mental illnesses: unipolar severe depression, acute suicidal tendencies, bipolar affective disorder, unipolar manic episodes, psychotic disorder, alcohol or substance use disorder (assessed using the Web-Based Screening Questionnaire (WSQ) [53], and Beck Depression Inventory–II (BDI-II) [54]Receiving CBT treatment, current or in the past 2 yearsRegular intake of benzodiazepines, changes in intake (e.g., start/change in dosage/discontinuation) of antidepressants or hormonal contraceptives within the last 3 monthsCurrent or planned IUI, IVF, or ICSI treatment with hormonal stimulation within the next 8 monthsCurrent pregnancy or birth of a child within the last 6 months, breastfeeding within the last 6 monthsCurrent diagnosis of one of the following: malignant tumor, esp. breast cancer, cervical cancer, or ovarian cancer; ulcerative colitis; Crohn’s disease; or any bacterial or viral infection such as TC, HAV, HBV, or HCV

### Who will take informed consent? {26a}

Informed consent will be obtained through local researchers experienced in working with patients with endometriosis. Potential trial participants receive detailed written information about trial scope, time schedule, randomization process, and so forth. During an extensive discussion of general trial benefits and risks, as well as use of trial participation via telephone, potential participants will be given the chance to address individual questions and concerns. Afterwards, participants will be asked to send written informed consent within the next few days to ensure that consent is given voluntarily without situational pressure.

### Additional consent provisions for collection and use of participant data and biological specimens {26b}

After trial completion, participants will be asked if they agree to be contacted in the future about further research participation. No collection of biological specimens is planned.

### Interventions

#### Explanation for the choice of comparators {6b}

The comparator is a waitlist control. Patients in the waitlist control group can continue with their usual treatment plan during trial participation (e.g., medication or physiotherapy). Because there is, as yet, no established treatment as usual (TAU) for patients with endometriosis, using a waitlist control seemed reasonable to capture real-life conditions. Patients currently receiving psychotherapy or seeking psychotherapeutic treatment in the past 2 years will be excluded from trial participation.

#### Intervention description {11a}

The online intervention lasts 8 weeks with one assigned interactive module per week, each of which consists of psychoeducational information, exercises, and homework. Different formats, methods, and media (e.g., infographics, videos, audio files, and text) will be used to convey relevant knowledge and strategies. For greater vividness, four fictional personas are introduced in the beginning; their answers and thoughts on certain exercises are displayed as encouraging examples. The intervention content was developed with helpful support from researchers with different scientific backgrounds and expertise in psychology, medicine, and gender studies. Additionally, the first three modules were tested by five endometriosis patients interested in iCBT. They were interviewed about their experience and provided valuable feedback on usability, psychoeducational comprehensiveness, and overall benefit.

Participants generate an individual biopsychosocial model about the impact of endometriosis on different areas of life and get to learn about cognitive restructuring. Relations between stress and pain are explored, and participants are encouraged to try out different pacing and relaxation methods. Acceptance and regulation of difficult emotions are practiced, as well as communication of healthy boundaries in different social settings. The last module focuses on reflection and long-term maintenance of achieved progression. Table 1 describes the intervention content in detail.

**Table 1 Tab1:** Content of the different modules

Week	Module name	Module content
1	**Module 1:** Getting started with the training	Psychoeducation, goal setting
2	**Module 2:** Thoughts I—Our constant companions	Cognitive restructuring I—Using the ABC model
3	**Module 3:** Thoughts II—Who controls whom?	Cognitive restructuring II—Using the ABCDE model
4	**Module 4:** My pain and me—And still I want to do something	Dealing with acute pain, pacing, weekly schedule
5	**Module 5:** Stress and pain—Always everything at once	Stress management (recovery skills, dealing with acute stress, contingency plans)
6	**Module 6:** Emotions—Accepting and tolerating	Psychoeducation, accepting and regulating negative emotions, mindfulness
7	**Module 7:** Clear communication	Basic communication rules, flexible handling of different situations
8	**Module 8:** My plan for the future	Summary, setting of long-term goals

Participants are asked to spend 1 to 2 h on each module. After each week, participants receive written feedback from a trained psychologist based on their input into the treatment platform. The participants can ask questions regarding the module they have been working on via text messages to their psychologist on the online platform. The psychologist is at least a bachelor-level clinical psychologist and receives regular supervision by a licensed CBT therapist.

#### Criteria for discontinuing or modifying allocated interventions {11b}

There are no criteria for discontinuing or modifying the intervention. Participants may withdraw from voluntary trial participation at any point for any given reason. Withdrawal from participation has no negative consequences or disadvantages for the participant. The investigators might also terminate participation if severe adverse events arise during the intervention.

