#### Process evaluation

To evaluate the planned CBT treatment and for identification of elements to focus on for further improvement, the participants are asked to provide weekly feedback on the module. We will therefore monitor symptoms and impact on HRQoL weekly throughout the training and present the questionnaire alongside a section for further comments on the module and aspects that have been helpful or unnecessary for each participant. Negative effects of treatment will be measured post-treatment and at follow-up.

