#### Endometriosis-related quality of life

For a quick assessment of HRQoL, the Endometriosis Health Profile-5 (EHP-5) [67] will be used weekly after each module. This 5-item short form of the EHP-30 + 23 provides sufficient reliability and validity [67].

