### Data collection and management

#### Plans for assessment and collection of outcomes {18a}

Data will be assessed online via self-report measures. Primary and secondary outcomes will be assessed at baseline, post-treatment, at a 3-month follow-up and, for the intervention group, at a 12-month follow-up. Control variables will be assessed at baseline only; measures for process evaluation will be assessed weekly during treatment and at post treatment as well as follow-up. For more details on outcome measures see {12}.

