#### Plans to promote participant retention and complete follow-up {18b}

Participants will be contacted for follow-up via e-mail. The data are collected online, reducing as many barriers as possible (e.g., having to schedule an in-person appointment or sending the questionnaires back). There is no additional incentive for participants to complete the trial. Based on our experience working with patients who suffer from endometriosis, the sample is usually grateful for any research conducted on endometriosis and tends to be very eager to participate.

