#### Adverse event reporting and harms {22}

Adverse events (AEs) will be collected and monitored by the therapists running the intervention. Any disadvantageous event occurring during the trial (e.g., worsening of symptoms, acute suicidal ideation, hospitalization due to mood deterioration) will be classified as an adverse event. Both AEs that are assumed to be a consequence of treatment and those that are not causally related to the treatment will be collected. All AEs will be discussed weekly regarding causality and severity, and possible further actions will be considered.

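### Section {11b} reads as letting investigators end trial participation after severe adverse events, with nothing to keep those participants under assessment; outcomes and NEQ scores could be lost, mainly in the iCBT arm

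*Protocol article*

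**What the plan says.** Section {11b} of the protocol article opens by stating that no stopping or modification criteria exist for the intervention. It continues "Participants may withdraw from voluntary trial participation at any point for any given reason", adds that withdrawal brings no disadvantage, and ends "The investigators might also terminate participation if severe adverse events arise during the intervention".

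The statements on follow-up elsewhere are general:

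- Abstract, Methods: "All participants will be followed up 3 months after the intervention".
- {18a}: "Primary and secondary outcomes will be assessed at baseline, post-treatment, at a 3-month follow-up", with a 12-month assessment for the intervention group.
- {18b}: "Participants will be contacted for follow-up via e-mail".

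On harms and process measures:

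- Process evaluation: "Negative effects of treatment will be measured post-treatment and at follow-up". The instrument is the NEQ.
- The short EHP-5 "will be used weekly after each module".
- {22}: "Adverse events (AEs) will be collected and monitored by the therapists running the intervention".

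On analysis, {20a} commits to intention-to-treat (ITT), includes anyone with at least one measurement, and plans sensitivity analyses for missing data. {20c} does not intend imputation and mentions multiple imputation under missing-at-random only as a possibility. {17a} leaves researchers and participants unblinded. {31c} states that no protocol exists beyond this article.

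**The concern.** Ending treatment and ending observation are separate decisions. ITT needs the second to continue when the first is taken. Section {11b} appears to merge them: the only investigator-initiated action it describes is ending participation, and no section provides for stopping the modules while staying under assessment.

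The resulting gaps would be informative. The trigger is a severe adverse event, for which {22} gives worsening symptoms, acute suicidal ideation and hospitalization for mood as examples of adverse events. The event must arise while the intervention is running, and the people who collect adverse events are the therapists delivering it. Removals would therefore fall mainly on the iCBT arm, among participants doing badly.

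Two things are at stake: a bias towards iCBT in the primary comparison, and the absence from the NEQ of the participants who may have most to report.

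**Working it through.** **Step 1. What does the sentence mean?** Three features of {11b} point to the trial. The preceding sentences concern withdrawal from trial participation. The word *also* carries that subject forward. And if the last sentence meant stopping the modules, it would itself be a criterion for discontinuing the intervention, which the opening sentence says does not exist. Two features point the other way: the section heading concerns the allocated intervention, and the event must occur during it. Removal from the trial is the more natural reading, but not the only one.

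**Step 2. Does another section rescue it?** The Abstract, {18a} and {18b} set a default of assessing everyone but do not mention participants whose participation was ended. Inclusion under {20a} on one measurement keeps such a participant in the model through her baseline alone; it supplies no post-baseline outcome. Given {31c}, the gap cannot be assumed to be filled in a fuller protocol.

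**Step 3. What is lost and what stays?** For a removal during treatment, the post-treatment and later EHP-30 + 23, pain, PDI and NEQ are lost. The triggering adverse event and the weekly EHP-5 scores up to that point stay on record.

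**Step 4. Size of the bias in the primary comparison.**

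Inputs from the plan: 120 participants and f = 0.25 ({14}), 1:1 allocation ({8}), two-sided 5% ({20a}). Hence 120/2 = 60 per arm. Reading f = 0.25 as a two-group effect gives d = 2 × 0.25 = 0.5 SD. The point does not depend on how 120 was derived.

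Assumptions, because the plan gives no severe-event or termination rate: k = 1 or 2 iCBT participants are removed before any post-baseline assessment, and their outcomes would have been d = 0.5, 1 or 2 SD worse than predicted from baseline. The 0.5 SD value represents events that affect mood more than pain or endometriosis-related quality of life.

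Shift in favour of iCBT = (k/60) × d:

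| Removed | d = 0.5 | d = 1 | d = 2 |
|---|---|---|---|
| 1 | 0.008 SD | 0.017 SD | 0.033 SD |
| 2 | 0.017 SD | 0.033 SD | 0.067 SD |

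The largest value is 0.067/0.5 = 13% of the planned effect. Against the unadjusted standard error √(2/60) = 0.183 SD, it is 0.067/0.183 = 0.37 standard errors.

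As a stress case only, removing 5% or 10% of the arm (3 or 6 of 60) with deficits of 0.5 to 1.5 SD gives 0.025–0.075 or 0.05–0.15 SD. Nothing in the plan supports rates that high.

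**Step 5. Effect on the false-positive rate.** A null simulation used 20,000 runs per cell, 60 per arm, three time points and all correlations 0.5 (assumed). In each arm k participants worsen by d at both later times; the k in iCBT give baseline only and stay in the model. Total two-sided rejection rates at a nominal 5%, with Monte Carlo error of about 0.15 percentage points:

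| Model | k = 0 | k = 1, d = 1 | k = 1, d = 2 | k = 2, d = 1 | k = 2, d = 2 |
|---|---|---|---|---|---|
| (a) Likelihood-based difference in change, baseline to 3 months | 5.2% | 4.9% | 4.9% | 5.0% | 5.6% |
| (b) Baseline-adjusted mean of post-treatment and 3 months | 4.8% | 5.1% | 5.3% | 5.4% | 6.2% |

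Under model (a), rejections favouring iCBT (nominally 2.5%) are 2.9% and 3.5% for one removal and 3.5% and 4.7% for two. Simulated shifts match the formula: for k = 2 and d = 2 they are 0.066 and 0.067 SD.

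**Step 6. NEQ.** Each removed participant who is not assessed later has no NEQ score: 1/60 = 1.7% or 2/60 = 3.3% of the arm's intended forms.

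**The case against.** The strongest reply is that the harm rests on one reading of an ambiguous, discretionary sentence and on events whose frequency is unknown. The heading of {11b} concerns the intervention, the general statements point to continued assessment, and no section says that questionnaires stop. All of that is fair, and it limits confidence in the reading. It does not remove the gap, because none of those statements addresses a participant whose participation has been ended.

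The numerical effect on the primary comparison is small, and the top of the range needs two removals, both before any post-baseline assessment and both 2 SD worse than predicted. That stands. The eligibility criteria exclude severe depression, acute suicidality, and bipolar and psychotic disorders, so few such events are likely. A participant in hospital may also not answer an e-mailed questionnaire, so rewording would recover only part of the loss.

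The NEQ is a process measure, and {22} records adverse events separately, whether or not they are treatment-related. That also stands: the harm itself would not vanish. But a recorded event does not replace a score on the questionnaire chosen to measure negative effects. That removed participants would report more of them is plausible, not shown.

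The sensitivity analyses in {20a} help only in part. The one method named, imputation under missing-at-random, is doubtful when removal follows an adverse event that the outcome model does not contain. No later analysis plan can recover questionnaires that were never sent.

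Lack of blinding adds little here, since the trigger is a clinical event.

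**Conclusion.** The concern holds as a minor point. On its most natural reading, {11b} allows removal from the trial after a severe adverse event, and nothing in the article keeps such a participant under assessment. With one or two removals from an arm of 60 and deficits of 0.5 to 2 SD, all assumed, the bias towards iCBT is 0.01 to 0.07 SD and the overall false-positive rate hardly moves. The primary conclusion is not materially threatened. The clearer cost is to the harms assessment: each removed participant who is not assessed later has no NEQ score. Confidence is moderate, because the sentence can also be read as stopping the modules only; under that reading no data need be lost.

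**What to change.** Reword {11b} so that investigators may stop the allocated intervention for severe adverse events. Add that anyone who stops the modules, for whatever reason, is still sent the post-treatment and 3-month questionnaires and, in the iCBT arm, the 12-month questionnaires, including the NEQ where scheduled, unless she withdraws consent to data collection. When to stop the modules remains the investigators' clinical decision.

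The cost is a wording change in {11b} and in the consent text, notified to the ethics committee as {25} already provides. The questionnaires are online and follow-up contact is by e-mail, so no new procedure is needed.
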